#### Statistical Analysis

We will conduct an ITS analysis, similar to the one performed previously [21,22]. ITS is considered a strong study design when randomization is not possible and can thus be used to investigate causal effects with an observational “natural experiment” approach. The Cochrane collaboration guidelines for ITS analyses will be used with an autoregressive integrated moving average model [23]. Because such a model relies on linearity, we will assess the stationarity of the mean and variance with time through differencing [24,25]. The primary analysis involves a comparison of inappropriate catheter usage before and after Participatient implementation. Because other changes in catheter usage could affect our outcomes over time, we will adjust the data for potential confounders, autocorrelation, and the underlying secular trend. Subgroup analyses will be performed on the basis of risk factors for catheters and UTIs, including the ward of admission, age group, internet or app use, and gender. Analyses will be conducted using SPSS (version 24, IBM Corp).

We will use figures to visualize trends and the impact of the intervention. We will present the difference in unadjusted and adjusted rate ratios with a 95% CI. Differences will be considered significant when *P*<.05. All analyses, including subgroup analyses, will be predefined in an analysis plan before their performance.

For questionnaire assessment, we will use descriptive statistics and compare patient satisfaction with health care, their involvement in care, and their trust in physicians, before and after implementing the app. Data on patient satisfaction regarding the usefulness and ease of use of Participatient will be analyzed using descriptive statistics and will be used for subsequent rounds of app improvement after the study.

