### Analysis

#### Sample Size

The sample size is based on our objective of reducing inappropriate catheter use by 15%, with a power of 80% and a Cronbach *α* of .05. We extracted data on the incidence of inappropriate catheter use from previous studies in similar health care systems, which was approximately 40% for catheters [17,18]. We aim to collect 9-12 data points from among 100 patients per survey date per hospital [19,20]. On designating a particular day to obtain measurements every 14 days at each center, a 5-month period before and after the measurements is required. We intend to carry out surveys for 6 months and to collect 12 data points. At the LUMC, the prevalence of catheter use is approximately 30% among hospitalized patients, based on our pilot survey. Thus, 1200 patients are required per period, of whom catheters were used for 400 patients, and catheter usage being inappropriate among 160 patients. On correlating for 10%-15% of the missing data, the sample size is set to 1320-1380 patients in the pre- and postintervention groups. We intend to include this number of patients at each hospital to analyze the effect of the interventions at each medical center.

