## Results

Based on our objective of reducing the inappropriate use of approximately 40% of catheters by 15%, we aim to collect 9-12 data points from among 70-100 patients per survey date per hospital. We will conduct an ITS analysis, which is considered a strong study design when randomization is not feasible. We will present the difference in unadjusted and adjusted rate ratios with a 95% CI. Differences will be considered significant when *P*<.05.

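### ARIMA with differencing on 18-24 survey points per hospital does not by itself give the promised rate ratio, and can lose much of the precision for the step

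*Protocol article*

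**What the plan says.** All in the protocol article.

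- **Model** (Statistical Analysis): "The Cochrane collaboration guidelines for ITS analyses will be used with an autoregressive integrated moving average model". The next sentence gives linearity as the reason for looking at stationarity, and continues: "we will assess the stationarity of the mean and variance with time through differencing".
- **Comparison and adjustment** (Statistical Analysis): "The primary analysis involves a comparison of inappropriate catheter usage before and after Participatient implementation". The authors add that "we will adjust the data for potential confounders, autocorrelation, and the underlying secular trend".
- **Reporting** (Statistical Analysis, repeated in Results): "We will present the difference in unadjusted and adjusted rate ratios with a 95% CI". The sentence after it calls differences significant at P<.05.
- **Data** (Sample Size): "We aim to collect 9-12 data points from among 100 patients per survey date per hospital", and then "We intend to carry out surveys for 6 months and to collect 12 data points". Results gives a wider range, "9-12 data points from among 70-100 patients per survey date per hospital". Sample Size puts catheter prevalence at about 30% and inappropriate use at about 40% of catheters, and intends an analysis at each centre.

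No outcome scale, log transformation or count model is stated. ARIMA orders and the intervention term are not given either, but they may properly sit in the analysis plan that the article announces. Their absence is not part of this point.

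**The concern.** Three stated choices do not fit together.

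1. **Scale.** Fitted to survey proportions, an ARIMA model gives a change in percentage points. The promised measure is a rate ratio, and nothing in the text links the two.
2. **Stationarity.** Differencing changes the series; it does not assess it. Linearity is also not why stationarity is needed. The practical risk is that a successful intervention shifts the mean. A check on the whole series can take that shift for non-stationarity and lead to differencing just when there is an effect to estimate. With so few points, choosing the orders that would repair this is fragile.
3. **Reported quantity.** Read literally, the interval describes how far adjustment moves the rate ratio. That measures confounding, not the effect of the app.

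At stake are the precision, the scale and the significance rule of the primary result.

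**Working it through.** **Inputs.** 12 surveys per period of 100 patients gives 12 × 100 = 1200, which reproduces the article's patients per period. At 30% prevalence that is 30 catheters per survey. Points per hospital: 2 × 9 = 18 to 2 × 12 = 24. Baseline 40%. The article does not say whether the 15% reduction is absolute (40% to 25%) or relative (40% to 34%, since 0.40 × 0.85 = 0.34), so both are shown. The article gives no power figure for the ARIMA model to reproduce.

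**Noise of one point.** σ = √(0.40 × 0.60 / 30) = 0.089, or 8.9 percentage points.

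**Standard error of the step, 12 + 12 points.**

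- Level only: σ√(1/12 + 1/12) = 0.408σ = 3.7 points.
- Segmented (time, step, slope change): least squares gives 0.82σ = 7.3 points.
- Differenced once, step differenced too, no moving-average term: the step becomes a single pulse, estimated from the two surveys either side of it. The error is σ√2 = 12.6 points. With a drift term it is 1.48σ = 13.2 points.

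**Approximate power, Φ(effect/SE − 1.96), one hospital.**

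| Model | SE (points) | 40% to 34% | 40% to 25% |
|---|---|---|---|
| Level only | 3.7 | 38% | 98% |
| Segmented with trend | 7.3 | 13% | 53% |
| Differenced, no moving-average term | 12.6 | 7% | 22% |

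Simulation agrees for 40% to 25%: 55-59% for segmented regression and 22-24% after differencing without a moving-average term. With 9 + 9 points, the same column reads 94%, 42% and 22%.

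**Four hospitals pooled, 40% to 34%.** The errors halve. Segmented: Φ(0.06/0.0367 − 1.96) = 37%. Differenced without a moving-average term: Φ(0.06/0.0632 − 1.96) = 16%.

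**Does a true step trigger differencing?** Share of simulated 12 + 12 series judged non-stationary:

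| Check | No effect | 40% to 25% |
|---|---|---|
| Dickey-Fuller, lag 0 | 1% | 40-41% |
| Dickey-Fuller, lag 1 | 26% | 94% |
| Dickey-Fuller, lag by AIC (two runs) | 9% and 35% | 67% and 65% |
| KPSS | 7% | 72% |

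The levels depend heavily on the lag. The direction is the same throughout. For 40% to 34% at lag 0 the share was only 4%, so the trap matters mainly for a large effect.

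**Can the proposed replacement hold its error rate?** One hospital, 24 points, no effect, step plus slope change: Poisson regression with uncorrected robust errors gave about 11-12% false positives. Binomial model-based or dispersion-scaled errors with a t reference held about 5%.

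**The case against.** A reader might infer two stronger statements: that ARIMA cannot produce a rate ratio, and that differencing removes the step. The documents support neither.

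- **Rate ratio.** The outcome scale is not fixed. A step fitted on the log scale and exponentiated is a ratio: simulations with a true ratio of 0.85 returned 0.83 to 0.86.
- **The step survives.** If the step term is differenced with the outcome, it stays estimable without evident bias; for a true change of −0.15, mean estimates were −0.14 to −0.15. The step would be lost if, for example, pre and post means of the differenced series were compared, and the article does not say that.
- **A moving-average term repairs most of the damage.** An ARIMA(0,1,1) without trend rejected in 91% (40% to 25%) and 36% (40% to 34%), close to the level-only model. This stands, with a limit. The article commits to adjusting for secular trend, and with trend in the model even a perfectly matched moving-average term only returns the undifferenced trend model, at about 53%. The term must also be identified from 18-24 noisy points.
- **Differencing is not fixed.** The text gives no order and no rule for applying it, and the analysis plan is not shown. This stands, so the power loss is a risk that the wording invites, not a certainty.
- **The reporting sentence may be loose English** for two ratios, each with its interval. That is plausible, since the primary analysis is defined as a before-after comparison. But the sentence appears twice and should say what is meant.
- **False positives do not favour one side.** ARIMA fits with autoregressive errors gave about 8-10%, and segmented Poisson with uncorrected robust errors was no better. The replacement needs the correction given under the fix.

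**Conclusion.** The point holds in limited form. The article fixes a model class, uses differencing as its stationarity check, and words the reported quantity in a way that does not match the promised effect measure; an analysis plan that follows the article would inherit all three. Differencing without a well-identified moving-average term would cut power for 40% to 25% in one hospital from about 53-59% to about 22-24%. The standard error of the step would be 12.6/7.3 = 1.7 times that of the segmented model.

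These figures assume independent binomial points, 30 catheters per survey, an abrupt step, equally spaced surveys with no gap for the implementation phase, and no true trend or autocorrelation. With 70 patients per survey (21 catheters), σ rises to √(0.24/21) = 0.107 and every standard error grows by the same factor. Real autocorrelation would change the figures. The rates at which a step triggers differencing should be read for direction only.

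**What to change.** Rewrite the primary analysis as follows.

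- **Model:** segmented log-link regression of inappropriate catheters out of catheters surveyed (log-binomial, or Poisson with dispersion-scaled errors). Include hospital, time, post-launch step and slope change. The adjusted model adds age group, gender and specialty, which the surveys already collect.
- **Standard errors:** dispersion-scaled or small-sample-corrected, with a t reference. Do not use uncorrected robust errors on 24 survey points. Check residual autocorrelation.
- **Reporting:** the unadjusted and the adjusted step rate ratio, each with its own 95% CI. Apply P<.05 to the adjusted one. Correct the sentence in both Statistical Analysis and Results.
- **ARIMA:** keep it as a sensitivity analysis, with its outcome scale stated and any differencing decided on the residuals after the step is fitted. Drop the wording that presents differencing as the assessment of stationarity.

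Cost: changes to the analysis text and a little more analysis work. No new data are needed, and the generalized linear procedures in SPSS, the named software, can fit the model.

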## Results

Based on our objective of reducing the inappropriate use of approximately 40% of catheters by 15%, we aim to collect 9-12 data points from among 70-100 patients per survey date per hospital. We will conduct an ITS analysis, which is considered a strong study design when randomization is not feasible. We will present the difference in unadjusted and adjusted rate ratios with a 95% CI. Differences will be considered significant when *P*<.05.

## Discussion

This protocol describes the objectives, design, intervention, and survey methods for the “Patient Engagement Counter Catheter-associated urinary tract infections with an App” study and aims to prevent the inappropriate and prolonged use of catheters at acute care facilities.

A potential limitation of an ITS analysis is the lack of a control group. However, this quasi-experimental design is considered to be among the most effective and powerful designs when randomization is not feasible. Another limitation of this protocol is its inability to evaluate the impact of app use on an individual level. However, the intervention stimulates communication and creates awareness regarding the risks of inappropriate catheter use among all ward staff through patient engagement, thus benefiting all patients in the ward.

Thus far, patient involvement in infection prevention has been undervalued and unused as a means to improve the quality of care. By sharing reliable information and daily checklists to patients via an app, we can provide them a tool to involve them in the management of catheter use. Thus, inappropriate catheter use is expected to be better noticed and discouraged, and the risk of CAUTIs could be reduced.

## Appendix

Multimedia Appendix 1 Reviewer Comments B.2017.01BA0 from The Netherlands Organisation for Health Research and Development (ZonMw): project 522004007, dossier number 50-52200-98-559.

Multimedia Appendix 2 Reviewer Comments B.2017.01BA1 from The Netherlands Organisation for Health Research and Development (ZonMw): project 522004007, dossier number 50-52200-98-559.

Multimedia Appendix 3 Reviewer Comments B.2017.01BD2 from The Netherlands Organisation for Health Research and Development (ZonMw): project 522004007, dossier number 50-52200-98-559.

## Abbreviations

CAUTI: catheter-associated urinary tract infection
ITS: interrupted time series
LUMC: Leiden University Medical Center
UTI: urinary tract infection
